## Abstract

**Background:**

Psychosis, even in its early stages, is associated with significant disability, causing it to be ranked ahead of paraplegia and blindness in those aged 18–35 in terms of years lived with disability. Current pharmacological and psychological interventions intervention have focused primarily on the reduction of positive symptoms (hallucinations and delusions), with little benefit to domains of psychosis such as cognitive difficulties and social and occupational functioning.

**Methods/design:**

The CReSt-R intervention trial is a single center, pilot randomised controlled study based at the National University of Ireland (NUI), Galway. The trial will recruit participants from four clinical sites with assessment and intervention completed by the primary NUI Galway team. The trial will explore the feasibility, acceptability, and effectiveness of a novel psychosocial intervention for early psychosis based on a combined cognitive remediation training and cognitive behavioural therapy approach focused on social recovery. Participants, aged 16–35 within the first 5 years of a diagnosed psychotic disorder, will be recruited from the Children and Adolescent Mental Health Service and the Adult Mental Health Services in the region.

**Discussion:**

Cognitive remediation training (for improving cognition) and social recovery focused cognitive behavioural therapy, have both separately demonstrated effectiveness. This trial will evaluate the feasibility, acceptability, and explore the efficacy of a treatment approach that combines both approaches as part of an integrated, multicomponent intervention.

**Trial registration:**

Cognitive Remediation & Social Recovery in Early Psychosis (CReSt-R): ClincialTrials.gov Identifier NCT04273685. Trial registered Feb 18^th^, 2020. Last updated April 14^th^, 2021.

## Background

In psychosis spectrum disorders, there has been a shift in focus from research and development focused purely on pharmacological symptom management to a focus on the broader concept of recovery. Although anti-psychotic medications have been effective in symptom remission, less than half of all schizophrenia patients have been able to achieve recovery [1]. Residual impairments in both neurocognition and social cognition, unaddressed by pharmacological intervention, continue to have a significant impact on function and the rate of disability in those living with psychosis [2, 3]. The rate of development of new pharmacological interventions has slowed with no new drug released to the market in approximately 20 years.

While cognitive deficits and their impact on the social and occupational functioning are well established in chronic schizophrenia, their effects in early psychosis (defined as within the first 5 years of a diagnosed psychotic disorder) are less well understood. A meta-analysis recently published by our group explored cognitive predictors of social recovery in early psychosis using cross-sectional and longitudinal data. The meta-analysis comprised 46 studies including 3767 participants and was based on nine cognitive domains. All cognitive domains were related to psychosocial function both cross-sectionally and longitudinally. These associations remained significant even after the effects of symptom severity, duration of untreated psychosis (DUP) and length of illness were accounted for. General cognitive ability (IQ) and social cognition were most strongly associated with both concurrent and long-term function [4].

To understand the relationship between *remission* and recovery in early psychosis, remission has been defined as referring to symptomatic and/or functional improvement over a > 6-month time frame and using specific assessment criteria (The Remission in Schizophrenia Working Group RSWG criteria). *Recovery* on the other hand was defined as symptomatic and functional improvement in social, occupational, and educational domains over a time frame of > 2 years [5]. In their meta-analysis of long-term outcome studies of first episode psychosis (FEP) 58% of participants met remission criteria at a mean of 5 years and 38% met recovery criteria at a mean of 7.2 years.

Key elements of recovery from an individual perspective have been identified as including connectedness, hope, identity, empowerment, and having a meaningful role [6]. However, these concepts are difficult to operationalise and quantify at a service level and so may get ‘lost in translation’ using conventional outcome measures, such as hospital admission rates, symptom reduction or global level of functioning.

In a systematic review and meta-analysis of 31 studies, we [7] investigated the impact of current psychosocial intervention on social and occupational functioning (both global and individual). We found that cognitive remediation training (CRT) was associated with significant gains in function, similar to chronic schizophrenia. CRT is defined as ‘a behavioural training-based intervention that aims to improve cognitive processes [attention, memory, executive function, social cognition, or metacognition] with the goal of durability and generalisability’ (‘Cognitive Remediation Experts Workshop (CREW)’, Florence, April 2010).

Cognitive Behavioural Therapy for psychosis (CBTp) is an evidence-based talking therapy with the primary aim of reducing clinical symptom severity, e.g. hallucinations and reducing relapse rates. This type of therapy was not significantly associated with improved social and occupational functioning. However, CBT focused on social recovery, social recovery therapy (SRT), was associated with significant improvements. Multicomponent interventions were found to be associated with the strongest gains in social and occupational functioning [7]. Across psychosis spectrum disorders, social cognition has been repeatedly linked to functional outcomes [8–11]. Social cognition is reported to mediate the effects of neurocognition on functional outcomes [2, 12–14].

Early intervention in psychosis (EIP) services are multi-disciplinary, clinical teams established to seek, identify, and reduce treatment delays at the onset of psychosis. They promote recovery by providing evidence-based intervention thereby reducing the probability of relapse following a first episode of psychosis. The concept, purpose, and effectiveness of *multicomponent intervention* in EIP has been described previously [15]. These interventions included the ‘core’ components of psychopharmacological treatment (with regular medication review) and family psychoeducation/counselling, alongside ‘optional’ components of CBT, family therapy, vocational and education counselling, social skills training, crisis management, and a crisis response team. Where does cognition fit in this multicomponent model?

Previously, in a review of social cognitive interventions, it was concluded that in order to impact higher-order social cognitive processes, there needs to be ample opportunity for practice of skills both in a clinical setting as well as in the community [16]. Social cognition is reported to mediate the effects of neurocognition on functional outcomes [2, 12, 14]. This suggests better functional outcomes may be achieved if both neurocognition and social cognition are targeted in intervention and that neurocognitive training alone does not result in significant social cognitive improvements [3, 14].

The CReSt-R study investigates a novel approach to optimising the cognitive and functional benefits of psychological interventions in early psychosis. It involves a multicomponent intervention that combines (a) CRT- a Computerised Interactive Remediation of Cognition-Training for Schizophrenia (CIRCuiTS) [17–19] with (b) social recovery therapy (SRT) [20–22]. In so doing, the aim is to target both social and occupational functioning and social cognition in young people living with psychosis, two outcomes of interest for this study.

CRT is recognised as an effective treatment in schizophrenia generally with a large meta-analysis reporting an effect size of Cohen’s *d* = 0.45 for cognitive performance, *d* = 0.42 for psychosocial functioning and *d* = 0.18 for symptom severity [23]. CRT programmes have evolved over the years with a variety of programme protocols and specific techniques now reported in the literature. An expert working group, identified four core features of CRT, including facilitation by a therapist, cognitive exercise, procedures to develop problem-solving strategies, and procedures to facilitate transfer to real-world functioning [24]. A meta-analysis supports this emphasis, finding that better outcomes following CRT were associated with an active and trained therapist, structured development of cognitive strategies, and integration with psychosocial rehabilitation [25]. The CIRCuiTS programme, outlined in the “Methods/design” section below, embodies these core elements. It is also informed by a metacognitive model, emphasising self-awareness, self-monitoring, and self-direction when completing the programme tasks and the transfer of these skills to everyday life.

SRT is informed by cognitive behavioural theory. It is an evolved form of cognitive behavioural therapy (CBT) with an emphasis on assertive outreach and behavioural experimentation. Similar to the CIRCuiTS programme it aims to apply cognitive work and newly acquired knowledge and strategies to everyday life with a focus on self-awareness and self-monitoring.

The CReSt-R study will contribute to the cognitive remediation field and the wider field of recovery in early psychosis by exploring the feasibility, acceptability, and effectiveness of this multicomponent psychosocial intervention with the hypothesis of a greater impact on social and occupational functioning and social cognition compared to treatment as usual in the target group. Whilst both intervention components have demonstrated efficacy in previous studies in addition to being found acceptable to participants [17–22], the acceptability of the combined, multicomponent intervention to young people aged 16–35 in the early psychosis population is unknown. In addition, the feasibility of delivering the multicomponent intervention and running a larger scale randomised control trial in Ireland is unknown.

## Methods/design

### Aims and objectives of the CReSt-R pilot randomised controlled study

The aim of the CReSt-R pilot randomised control study is to gather and analyse acceptability and feasibility data to (1) further develop and refine the novel, multicomponent CReSt-R intervention (2) investigate the feasibility of delivering and evaluating the intervention in future definitive trials. Specifically, the study objectives (outlined in further detail in “The CreSt-R intervention and control condition”, “Feasibility”, “Acceptability”, “Estimating treatment effect sizes” sections) include the following:To collect qualitative and quantitative data to assess the feasibility of the intervention with indicators in the areas of process, intervention, and resources.To investigate if the CReSt-R intervention is acceptable to young people, aged 16–35, who are within the first 5 years of a diagnosed psychotic disorder.To explore the effectiveness of the intervention by analyzing primary and secondary outcome data to provide treatment effect estimates, thus informing future trial design.

### Ethics, consent, and permissions

This study was approved by the Galway Clinical Research Ethics Committee, Merlin Park Hospital, Galway, Ireland. All participants will provide informed signed consent. The ethics application also detailed general data protection regulation (GDPR) considerations, the proposed management of vulnerable individuals in the study and assent for participants aged under 18 years of age.

### Setting and participants

This is a community-based study and will recruit participants from the Children and Adolescent Mental Health Service (CAMHS) and the Adult Mental Health Service (AMHS). Recruitment referrals from primary care providers and self-referrals are also accepted on a case-by-case basis with a primary clinical contact deemed essential for participation. Collaboration with clinical teams is anticipated to assist with recruiting adequate number of participants for this study. A sample size of 30 is a common ‘rule of thumb’ in pilot studies [26, 27], with 15 in the intervention arm and 15 in the control arm considered adequate in generating data to explore the feasibility and acceptability of the proposed intervention and in providing an estimate of the intervention’s efficacy for planning a definitive intervention trial. This pragmatic approach is consistent with other feasibility studies in the area of early psychosis [28] and in line with current recommendations for pilot studies [29].

Inclusion criteria for the study are being aged between 16 and 35 years of age, within the first 5 years of a diagnosed psychotic illness (based on time since first contact with a clinical service), community based, clinically stable and having the ability to give consent. Exclusion criteria are having a history of organic impairment (including IQ < 70), history of a head injury with loss of consciousness > 5-min duration and drug abuse in the preceding month. Confirmation of diagnosis, timeframe of onset of psychotic symptoms, presence of cognitive and social and occupational difficulties will be provided via a referral form completed by the primary clinical contact. Participants may withdraw from the study at any time.

### Study design, randomisation, and treatment allocation

A randomised pilot study with a controlled, outcome-assessor-blind, parallel- group design will be implemented. Randomisation will use a permuted block design, using a computerised random number generator with predetermined 1:1 allocation ratio and will be completed by an independent statistician. The study research assistant will provide an information sheet to a potential participant and answer any questions they may have before obtaining written consent. There will be a 7-day cooling off period between provision of consent and enrolment to the study. Upon enrolment into the study the participants will be randomised to the intervention group (CReSt-R) or the control group. Both interventions are detailed below. After randomisation, the participant will complete baseline assessments with an assessor blind to treatment allocation. All participants will be instructed not to reveal their treatment allocation prior to each follow-up assessment. Should the blind be broken for any participant, this will be noted and reported to the principal investigator. The primary clinical contact for each individual participant will be informed of treatment allocation. The consort diagram for study procedure is contained in Fig. 1.

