### Estimating treatment effect sizes

To clarify, this study does not aim to determine treatment effect. However, to inform statistical power calculations for primary and secondary treatment outcomes in advance of a full RCT, estimates of treatment effect sizes will be obtained using linear mixed models. These analyses, completed in SPSS version 27, will provide a treatment effect estimate on each outcome measure at 2 and 12 weeks post-intervention. Outcome measures at these two time points will be entered into the model as the dependent variables with fixed effects of study arm, baseline outcome measures, time, and a time point by study arm interaction. Inclusion of baseline outcome measures accounts for their potential prediction of future outcome and will contribute towards accurate effect estimates. A random effect for participant will also be entered into the model to account for correlations between the two time points (repeated measures) per participant. This analysis will be carried out by the trial statistician.

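### Baseline is measured after randomisation while only the assessor is blind, and the effect model then adjusts for it, so T1 should be completed first or allocation withheld until it is done

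*Protocol article*

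**What the plan says.** In the Protocol article, the section on study design, randomisation and treatment allocation fixes the sequence. After consent and a 7-day cooling-off period, "Upon enrolment into the study the participants will be randomised to the intervention group (CReSt-R) or the control group". Then: "After randomisation, the participant will complete baseline assessments with an assessor blind to treatment allocation".

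The same section describes the blinding: "A randomised pilot study with a controlled, outcome-assessor-blind, parallel- group design will be implemented". On disclosure it says "All participants will be instructed not to reveal their treatment allocation prior to each follow-up assessment", and also "The primary clinical contact for each individual participant will be informed of treatment allocation". It does not say when the participant learns the allocation.

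The section on estimating treatment effect sizes takes the two post-intervention time points (2 and 12 weeks) as the dependent variables, with "fixed effects of study arm, baseline outcome measures, time, and a time point by study arm interaction". The reason given is that "Inclusion of baseline outcome measures accounts for their potential prediction of future outcome".

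The Feasibility section commits to intention to treat. Table 2 sets a retention target of 75% of those randomised to the intervention completing T1, T2 and T3. The article does not define T1, but with three outcome time points of which two are post-intervention, T1 must be baseline.

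**The concern.** A baseline covariate is safe to adjust for because it is measured before allocation can affect it. Here that protection is absent by design. Assessor blinding protects the rating but not the participant's own answers or effort. The Need for Cognition Scale is listed as self-report, and the cognitive and social-cognition tests depend on effort. Someone pleased or disappointed with their arm may perform or answer differently at T1. Because the non-disclosure instruction does not name T1, the participant may also tell the assessor their arm at that visit, before any follow-up has taken place.

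Three things are at stake:

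- **Effect estimates.** They are meant to inform power calculations for a full trial. A covariate that allocation has moved biases them.
- **The analysed set.** A participant randomised but never assessed at T1 has no covariate value, so the model as described cannot use their follow-up data. That sits badly with intention to treat.
- **The retention criterion.** It counts T1 among those randomised, so a loss between randomisation and T1 counts against progression. With T1 completed first, that loss would occur before randomisation.

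**Working it through.** **The plan's own figure.** The sample size is a rule of thumb: 15 + 15 = 30. This reproduces. The article states no alpha, power, SD or effect-size formula.

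**Inputs.**

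- From the article: 15 per arm; baseline as a fixed effect; baseline not among the dependent variables.
- As a yardstick only: d = 0.42 for psychosocial functioning, the meta-analytic figure for cognitive remediation in the Background. It is not a design input.
- Assumed, because the article gives neither: a baseline-to-outcome slope b of 0.3 to 0.7, and an allocation-caused shift s in T1 (intervention minus control) of 0.1 to 0.5 SD.

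**Formula.** Let the undisturbed baseline be x0, the outcome be b·x0 + d·arm + error, and the recorded baseline be x = x0 + s·arm. Substituting x0 = x − s·arm gives an arm coefficient, adjusted for x, of d − b·s. The bias is −b·s, opposite in sign to the shift.

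| Slope b | s = 0.1 | s = 0.2 | s = 0.3 | s = 0.5 |
|---|---|---|---|---|
| 0.3 | −0.03 | −0.06 | −0.09 | −0.15 |
| 0.5 | −0.05 | −0.10 | −0.15 | −0.25 |
| 0.7 | −0.07 | −0.14 | −0.21 | −0.35 |

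Against the yardstick, the ends of the range are 0.03/0.42 = 7% and 0.35/0.42 = 83%. If s is negative, the signs reverse.

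**Simulation check** (15 per arm, one follow-up time point, 8,000 replicates, true effect 0.42):

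- b = 0.5, s = 0.2: mean estimate 0.320 (formula 0.42 − 0.10 = 0.32)
- b = 0.7, s = 0.3: mean estimate 0.211 (formula 0.42 − 0.21 = 0.21)
- b = 0.5, s = 0, as when T1 precedes randomisation: mean estimate 0.418

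**Scale against sampling error.** The standard error of a standardised difference at one time point is √(2/15) = 0.365 unadjusted. With b = 0.5 taken as the correlation, it is 0.365 × √(1 − 0.25) = 0.316 adjusted. A bias of 0.10 is then 0.10/0.316 = 0.32 of one standard error.

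**Missing T1.** Each participant randomised without T1 removes 1/30 = 3.3% of those randomised from the model. In the intervention arm, each one lowers the T1–T3 completion rate by 1/15 = 6.7 percentage points.

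**The case against.** **Knowledge of the arm at T1 is not established.** A reader might infer that participants do know their arm at T1. The article does not say so. An independent statistician randomises, and an instruction confined to follow-up also fits allocation being disclosed only after T1. The consort diagram, which might settle it, is not shown. This objection stands, so the claim is only that participants can know. The stated procedure does not prevent it.

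**The link to the primary outcome is loose.** T1 is done with a blinded assessor, and expectation effects are easier to argue for self-report and effort-dependent tests than for the SOFAS. This also stands: how far any shift would reach the SOFAS is unknown.

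**The formula assumes the shift fades.** If a share k of the shift persists to follow-up, the adjusted estimate is displaced by s(k − b), not −b·s, so adjustment removes part of a persistent shift. The range above is conditional on k = 0.

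**Leavers.** A reader might infer that early leavers in general fall out of the model because of the ordering. They do not. The dependent variables are post-intervention only, so anyone who leaves before the first follow-up contributes nothing in either order. The ordering costs the model only those without T1 who are still followed up, and the analysis plan, not shown, may say how a missing baseline is handled. The Feasibility section also promises to describe missing data at all three time points, and Table 1 promises data on leavers by group.

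**Eligibility.** A reader might infer that people with IQ below 70 would be found only at T1, after randomisation. The exclusion is framed as a matter of past history, and nothing makes the T1 subtests a screening step. The inference is unsupported.

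**It is a pilot.** The article says it does not aim to determine treatment effect, and no effect estimate enters the progression criteria. That lowers the severity. It does not remove the point, because the estimates are meant for power calculations and T1 completion does enter a progression criterion.

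**Conclusion.** The concern holds as a weakness in a stated procedure. T1 follows randomisation, participants are not blinded, the disclosure rule leaves T1 uncovered, and the model adjusts for the T1 value. Under the assumed slopes and shifts, and if the shift does not persist, the adjusted effect is biased by 0.03 to 0.35 SD against the direction of the shift. Nothing in the article shows that such a shift will occur or how large it would be, so this range illustrates exposure and is not an estimate of actual bias. The effect of a missing T1 on retention, 6.7 percentage points per intervention participant, is arithmetic on 15 per arm; how many such participants there will be is unknown. An analysis method cannot restore a pre-randomisation baseline that was never taken, so this is best settled in the procedure. It should be fixed, but it does not invalidate the pilot.

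**What to change.** 1. Reorder the steps: consent, cooling-off period, T1, then randomisation once T1 is complete. Any allocation-caused shift in T1 is then zero by design, and everyone randomised has completed T1.
2. If that is not possible, withhold allocation from the participant until T1 is complete, state this in the protocol, and extend the non-disclosure instruction to T1. This deals with expectation and unblinding but not with losses between randomisation and T1.
3. The trial is ongoing. For participants already randomised before T1, keep them in the intention-to-treat set, report the number without a baseline by arm, and add a sensitivity analysis without baseline adjustment. A model that forces equal baseline means across arms is a poorer choice, because equal means are the assumption in doubt.

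**Cost.** Item 1 is a procedural amendment that swaps two existing steps. Its small downside is that T1 will occasionally be done on someone who is then not randomised. The article gives no visit schedule, so whether visit logistics change cannot be judged from it. The unadjusted analysis is less precise (standard error about 0.365 against 0.316 in the example above), which is why it belongs as a sensitivity analysis.
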